**Methods:**

A pre-post intervention study with a cluster design and one intervention group will be carried out in CPs in the canton of Vaud (Switzerland) for 15 months. Volunteer pharmacists will be trained on the identification and management of DRPs related to patients’ behavior. After training, they will include randomly selected adults taking four or more chronic drugs prescribed for at least three months prior to recruitment. Then, they will conduct three pharmacist-patient face-to-face consultations at 6-month intervals. Tasks will be differentiated by pharmacy technician or pharmacist to triage expired medication or to manage DRPs in a structured manner, respectively. The primary outcome is the identification of DRPs associated to patients’ behavior. Secondary outcomes are to assess patients’ medication knowledge, number of expired medications, interventions carried out by pharmacists and pharmacists’ satisfaction. The study will begin in April 2023 in 19 to 35 pharmacies that will recruit at least 162 patients. A sub analysis will be carried out for patients with 65 years old or over.

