Number of pharmaceutical interventions (quantitative)	Number of interventions carried out by the pharmacist to correct DRPs and/or prevent their consequence. Total number of interventions and mean per pharmacist, per patient, per number of medications and number of DRPs identified will be calculated.	Pharmacists will complete the PharmDISC tool before and during the consultation.
Pharmaceutical interventions classification (qualitative)	Classification of interventions will be made using PharmDISC tool: • Substitution • Dose adjustment • Adjustment of the delivery amount (package size, quantity of packages, etc.) • Optimization of administration / Change of administration way • Therapy stopped/no delivery • Therapy started • Counselling of patient • Application/use instruction (training) • Delivery of an adherence aid inclusive counselling • Clarification in the case notes (history) • Information to the GP • Therapy monitoring • -Other	Pharmacists will complete the PharmDISC tool before and during the consultation.
Pharmaceutical interventions acceptance (quantitative)	Pharmaceutical interventions acceptance by the patient or the GP (when proposed to the GP, it will be considered as accepted unless the GP states otherwise). Number and proportion of intervention accepted versus proposed according to the number of medications and the number of DRPs.	Pharmacists will complete the PharmDISC tool during the second and third consultation.
**Secondary outcomes**	**Definition and assessment**	**Time point**
Number of removed medications (quantitative)	Expired or in bad condition or unused medications will be identified after reviewing the medication brought by the patient to the pharmacy: total number, mean per patient and percentage in relation to the total medication brought by the patient will be documented.	Pharmacists will complete the medication plan during the consultation with patients.
Number of removed medications discharged (quantitative)	Number of medications proposed to be removed and accepted by the patient after pharmacist-patient consultation: total number, mean per patient and percentage in relation to the total expired medication identified will be documented.	Pharmacists will complete the medication plan during the consultation.

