### Statistical methods and analysis

Continuous variables will be summarized using mean and standard deviation, or median and percentiles depending on the distribution of the variable. To assess normality, the Kolmogorov Smirnov test will be used. Categorical variables will be reported by frequency and proportion. For the comparison of continuous variables, the T Student’s test or the ANOVA test will be carried out if there is a normal distribution, and Kruskal-Wallis otherwise. The comparison of the categorical variables will be carried out using the χ2 test, the Fisher’s exact test or Yate’s chi-squared test if necessary.

For each patient, differences between consultations (second and first consultations, third and first consultations) will be compared for dependent variables (number of DRPs and medication expired, patient knowledge score, pharmaceutical interventions and medication removed, proportion of pharmaceutical interventions acceptance). A linear regression model will be performed accounting for the cluster effect. A cluster effect is expected by the way pharmacists interact with their team and the surrounding GPs, this could influence the number and type of DRPs detected and interventions made. A sub analysis will be carried out to evaluate the effect of patients undertaking or not a pre-selection of their medication before attending the pharmacy. Firstly, variables will be considered significant (p-value<0.2) in a bivariate model to be included in a multivariate model. Secondly, the variables considered significant at a value of p<0.1 in the multivariate model will be included in the final model. The level of significance will be set at p<0.05; the software STATA 17® will be used. An analysis with completed cases will be made (patients with data for the three consultations). In addition, an analysis with the whole sample will be made where, for the management of missing data, initial value will be considered as not been modified (baseline observation carried forward-BOCF) [28]. In case of a sufficient number of patients who are 65 years old or over are randomly included in the study, a sub analysis will be carried out to target the intervention to a specific group of patients with higher risk for DRPs [29, 30].

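### As literally worded, the acceptance percentage for removed medications counts all removable items in the numerator but only expired items in the denominator, so it can overstate acceptance and exceed 100%

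*Protocol article*

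**What the plan says.** Two adjacent rows of Table 1 (protocol article, Study measurements and outcomes) deal with medication disposal; both are secondary outcomes.

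- *Number of removed medications* sets the class of items: "Expired or in bad condition or unused medications will be identified after reviewing the medication brought by the patient to the pharmacy". Its percentage has its own base: "percentage in relation to the total medication brought by the patient will be documented".
- *Number of removed medications discharged* counts the items the patient agrees to give up: "Number of medications proposed to be removed and accepted by the patient after pharmacist-patient consultation". Besides a total and a mean per patient, it fixes a "percentage in relation to the total expired medication identified".

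Two other places bear on how the word expired should be read. The Methods paragraph of the Abstract names the secondary outcome as "number of expired medications". Statistical methods and analysis lists the variables to be compared between consultations as "number of DRPs and medication expired, patient knowledge score, pharmaceutical interventions and medication removed", so expired and removed appear there as two items.

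**The concern.** The second row carries over the term removed medications from the row above, where it covers three kinds of item, and does not limit its count to expired ones. Its denominator names only the first kind. A ratio whose numerator is not contained in its denominator is not a proportion, and it need not lie between 0 and 100%.

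The article states this calculation rule in full, so it is not a detail left to an analysis plan. Taking expired medication out of the home is one of three aims given for the service in the Introduction. This percentage is the summary in the row that shows how often patients agree to disposal, since a total or a mean per patient has no base to judge it against. Two analysts could also report different percentages from the same data, one dividing by expired items and the other by all removable items.

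**Working it through.** The article gives no figure for this outcome, so there is nothing to reproduce. The check is on the definition.

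**Inputs from Table 1**

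- Removable items: expired (E), in bad condition (B), unused (U). Source: *Number of removed medications*.
- Numerator: accepted items (A), not restricted to expired ones. Source: *Number of removed medications discharged*. That A may include all three kinds is inferred from the shared term and the preceding row.
- Denominator as worded: E. Source: the same row.

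**Formulas**

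For simplicity, suppose every identified item is proposed for removal; the article does not say this.

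- As worded: A / E
- Matched: A / (E + B + U)
- Ratio of the two: (E + B + U) / E = 1/s, where s is the expired share of removable items

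Three results follow for E > 0:

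1. If A > 0 and B + U > 0, the worded figure is larger than the matched one, by the factor 1/s.
2. The worded figure exceeds 100% exactly when A > E, that is, when the acceptance proportion is greater than s.
3. The two agree for any A > 0 only when every removable item is expired.

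The worded figure also exceeds an expired-only acceptance rate (accepted expired items / E) whenever at least one non-expired item is accepted.

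**Illustrations (all counts assumed)**

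| E | B | U | Accepted | As worded | Matched |
|---|---|---|---|---|---|
| 10 | 0 | 0 | 8 | 8/10 = 80% | 8/10 = 80% |
| 10 | 2 | 3 | 12 | 12/10 = 120% | 12/15 = 80% |
| 3 | 1 | 4 | 6 | 6/3 = 200% | 6/8 = 75% |
| 5 | 2 | 8 | 12 | 12/5 = 240% | 12/15 = 80% |

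**Range over the unknown expired share, with every item accepted (true acceptance 100%)**

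| Expired share s | As worded (1/s) |
|---|---|
| 90% | 111% |
| 70% | 143% |
| 50% | 200% |
| 30% | 333% |

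The direction of the error does not depend on the counts chosen; its size does.

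**The case against.** The best defence is that expired is the article's everyday label for the whole disposal activity. The Abstract names the outcome that way, and the Introduction states the aim that way. The two variables listed in Statistical methods and analysis may simply be these two table rows: items identified, and items removed. On that reading the denominator means everything identified in the row above, numerator and denominator match, and the percentage cannot exceed 100%. The defence can add that it is uneven to carry the three-category class into the numerator while refusing it to the denominator of the same row.

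This has real weight. Nothing in the article rules the reading out, and the three-category numerator is itself an inference. But nothing states the reading either. The row directly above uses expired as one of three alternatives, and the analysis section lists expired and removed separately. If shorthand is what was meant, the denominator is still misnamed and should be reworded.

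A second defence is that the numerator is meant to be expired-only. That would make the term removed medications change meaning between consecutive rows, and the text would have to say so.

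Two further limits stand. A reader might infer that the percentage is undefined for any patient with no expired item. That assumes a percentage worked out patient by patient, whereas the row attaches per patient only to the mean; a pooled percentage would be undefined only if no expired item were found at all. A reader might also infer that the needed split by reason is already recorded. The medication plan is completed for these outcomes, but the form itself (S4 Appendix) is not shown.

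**Conclusion.** The point holds for the wording as it stands. Taken literally, the rule divides accepted items of any removable kind by expired items only. It therefore overstates acceptance whenever non-expired items are accepted, and can exceed 100%. This rests on two assumptions: that the second row covers the same class as the first, and that expired means expired. If expired is shorthand, the fault is one of wording, and the line still needs correcting.

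It would be going too far to say that the reported percentage will be wrong, or by how much. The article does not settle which reading the investigators will apply and gives no counts, so the 200% against 75% shows what is possible, not a forecast. The matter is minor. It affects one descriptive percentage of one secondary outcome; the total, the mean per patient, the primary outcome and the sample size are untouched.

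**What to change.** In the *Number of removed medications discharged* row, replace the denominator with all medications identified, or all proposed, for removal: expired, in bad condition and unused together. Say which of identified or proposed is meant, because the two differ if some identified items are not proposed. Using identified items ties the percentage directly to the count in the row above.

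If an expired-only acceptance figure is also wanted, restrict both numerator and denominator to expired items, and confirm that the form records the reason for removal.

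The cost of the main change is one line in Table 1. The all-items version needs no split by reason; with identified items as the base, its denominator is already the count in the row above. The expired-only version may need an extra field if the form does not already record the reason.

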### Sample size

Primary objective of the study aims to measure the difference in DRPs per patient observed between consultations. Sample size calculation was based on this primary study outcome to detect a difference of 0.5 DRP per patient at the end of the study (using a one-tailed test because the hypothesis is that patients will have a decrease of DRPs at the end of the study). The calculation was based on a pilot study carried out on 20 patients at Unisanté CP. Sample size was calculated with ≥0.8 power, type I error rate of 5%, assuming an intra-cluster correlation of 0.02. Allowing for 15% dropout, the overall sample size is 162 patients, with 19 to 35 pharmacies (5–10 patients per CP).

### Statistical methods and analysis

Continuous variables will be summarized using mean and standard deviation, or median and percentiles depending on the distribution of the variable. To assess normality, the Kolmogorov Smirnov test will be used. Categorical variables will be reported by frequency and proportion. For the comparison of continuous variables, the T Student’s test or the ANOVA test will be carried out if there is a normal distribution, and Kruskal-Wallis otherwise. The comparison of the categorical variables will be carried out using the χ2 test, the Fisher’s exact test or Yate’s chi-squared test if necessary.

For each patient, differences between consultations (second and first consultations, third and first consultations) will be compared for dependent variables (number of DRPs and medication expired, patient knowledge score, pharmaceutical interventions and medication removed, proportion of pharmaceutical interventions acceptance). A linear regression model will be performed accounting for the cluster effect. A cluster effect is expected by the way pharmacists interact with their team and the surrounding GPs, this could influence the number and type of DRPs detected and interventions made. A sub analysis will be carried out to evaluate the effect of patients undertaking or not a pre-selection of their medication before attending the pharmacy. Firstly, variables will be considered significant (p-value<0.2) in a bivariate model to be included in a multivariate model. Secondly, the variables considered significant at a value of p<0.1 in the multivariate model will be included in the final model. The level of significance will be set at p<0.05; the software STATA 17® will be used. An analysis with completed cases will be made (patients with data for the three consultations). In addition, an analysis with the whole sample will be made where, for the management of missing data, initial value will be considered as not been modified (baseline observation carried forward-BOCF) [28]. In case of a sufficient number of patients who are 65 years old or over are randomly included in the study, a sub analysis will be carried out to target the intervention to a specific group of patients with higher risk for DRPs [29, 30].

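### A Kolmogorov-Smirnov pre-test chooses between means and ranks for outcomes sized on a difference of 0.5 DRP per patient, and the plan does not say whether this comparison or the planned linear regression decides

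*Protocol article*

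**What the plan says.** Protocol article, Statistical methods and analysis, first paragraph: "To assess normality, the Kolmogorov Smirnov test will be used". The t test or ANOVA "will be carried out if there is a normal distribution, and Kruskal-Wallis otherwise". This rule covers continuous variables in general.

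Second paragraph of the same section: for each patient, "differences between consultations (second and first consultations, third and first consultations) will be compared for dependent variables", and the number of DRPs is among those variables. It continues: "A linear regression model will be performed accounting for the cluster effect". This model does not depend on the normality test.

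Protocol article, Sample size: the study is sized "to detect a difference of 0.5 DRP per patient at the end of the study". The calculation is one-sided, in the direction of fewer DRPs, with power of at least 0.8, a 5% type I error and an intra-cluster correlation of 0.02. After an allowance of 15% for dropout, the total is 162 patients. Table 1 reports the DRP count as a total and a mean per patient, so the 0.5 is most naturally read as a difference in means.

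**The concern.** The study is sized on one quantity, the average change in DRPs per patient. The pre-test lets the observed data decide whether the comparison concerns that quantity or a different one.

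The rank branch takes its null from equal distributions, not from a mean change of zero. If many patients lose a DRP and a few gain several, the average burden can be unchanged while ranks point to a decrease. If the fall sits in a few patients with many DRPs, ranks can miss a fall that the mean shows. The rank test named, Kruskal-Wallis, is also a test for independent groups. Applied to the consultations, it uses neither the pairing within patients nor the pharmacy clustering allowed for in the sample size.

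The linear regression can then give a different answer from the gated comparison, and the section gives neither precedence. The pre-test is not needed for the mean analysis either, because the mean of about 138 differences is close to normal even when the differences are not.

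**Working it through.** **1. The plan's own figure.** For a within-patient mean change, N = (SD × (1.645 + 0.842) / 0.5)² × [1 + (m − 1) × 0.02] / 0.85, where m is the number of patients per pharmacy (5 to 10). The protocol names a pilot of 20 patients as the source but gives no SD, so 162 cannot be recomputed, only solved backwards. Completers: 162 × 0.85 = 137.7.
- m = 5: 137.7 / 1.08 = 127.5, so SD = 0.5 × √127.5 / 2.487 = 2.27.
- m = 10: 137.7 / 1.18 = 116.7, so SD = 0.5 × √116.7 / 2.487 = 2.17.

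This is no evidence that 162 is wrong. It gives an SD of about 2.2 to 2.3 against which to set the assumptions below.

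**2. Which branch the pre-test selects.** Assumptions: 138 completers; Poisson or gamma-Poisson counts (gamma shape 2 or 1, shared by a patient's two visits); follow-up mean lower by 0.5; no pharmacy clustering; 400 runs per setting; pre-test at 5% with mean and SD estimated from the sample. Counts and changes are both shown because the rule could be applied to either. Ranges run over the three dispersions.

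| Assumed mean DRPs | KS rejects, counts | KS rejects, changes | Lilliefors-corrected, changes | SD of change |
|---|---|---|---|---|
| 1 | 100% | 100% | 100% | 1.22–1.30 |
| 2 | 100% | 88–100% | 100% | 1.87–1.92 |
| 3 | 99.5–100% | 42–99.8% | 99.8–100% | 2.34–2.39 |
| 5 | 82–100% | 13–97% | 91–100% | 3.09–3.12 |
| 8 | 41–100% | 3–82% | 67–100% | 3.91–3.94 |

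At means of 1 to 3 the rank branch is the usual one. At higher means the branch depends on dispersion, on the version of the test and on chance. The SD of 2.17 to 2.27 from step 1 lies between the rows for means 2 and 3. That is weak support for a low mean, because it holds only under this count model.

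**3. Whether the rank branch tests a mean change.** 4,000 runs, n = 138, all tests two-sided at 5% so that they are comparable, both visit means equal to 2:
- Same distribution at both visits, correlated: Kruskal-Wallis 0.3%, signed-rank 4.8%, paired t 4.9%.
- More spread at follow-up, correlated visits: Kruskal-Wallis 30.2%, signed-rank 8.6%, paired t 4.9%.
- More spread at follow-up, independent visits: Kruskal-Wallis 55.4%, signed-rank 14.8%, paired t 4.9%.

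The mean change is zero in all three, and only the paired t test stays near 5% throughout. Making the rank test paired reduces the problem but does not remove it.

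**4. Power for a true fall of 0.5, proportional in all patients.** Same settings:

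| Mean, gamma shape | Paired t | Signed-rank | Independent t | Kruskal-Wallis |
|---|---|---|---|---|
| 2, 1 | 86.5% | 84.1% | 45.7% | 34.3% |
| 2, 2 | 87.2% | 85.6% | 66.7% | 57.0% |
| 3, 1 | 70.3% | 67.1% | 11.4% | 8.9% |
| 3, 2 | 70.1% | 66.9% | 29.8% | 25.8% |

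From paired t to independent t the loss is 20.5 points (87.2 − 66.7) to 58.9 points (70.3 − 11.4). From independent t to Kruskal-Wallis it is a further 2.5 points (11.4 − 8.9) to 11.4 points (45.7 − 34.3). Most of the loss therefore comes from ignoring the pairing. The signed-rank test is only 1.6 to 3.2 points below the paired t test.

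**5. Uneven change.** These scenarios are constructed, with one-sided 5% tests.
- Mean change zero, 10–12% of patients gaining about 4 DRPs and the rest losing 0.5 on average: the signed-rank test rejects in 13% to 59% of runs, depending on how the losses are generated, and the mean test in 6% to 8%. Only the direction is secure.
- The whole fall of 0.5 confined to the 15% of patients with about 6 DRPs: power is 71% for signed-rank and 87% for the mean test.

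**The case against.** The strongest defence is that the powered question is already answered by the linear regression. It is mean-based, does not depend on the pre-test, directly follows the sentence on within-patient differences, and is the only method in the section said to account for clustering. The pre-test stands in a general paragraph on continuous and categorical variables, and nothing ties it to the 0.5 DRP difference. On this reading only the order of precedence is unstated, which a condensed article may leave to a fuller document.

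Much of this stands. A reader might infer that the plan never tests the powered difference; the regression contradicts that. A reader might also infer that the pre-test always selects ranks. The protocol gives no DRP mean or dispersion, and patients on four or more chronic drugs, screened for 15 DRP types, could average more than 3. At a mean of 8, uncorrected rejection on changes is 3–82%. Nor does the low power of Kruskal-Wallis measure the harm of ranks as such, since most of it is lost pairing. The scenarios of uneven change have no support in the document, and under a proportional fall a paired rank test and the mean test nearly agree.

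The defence does not remove the rule itself. The pre-test is stated, not left open. It covers continuous variables, the number of DRPs is classed as quantitative, and comparing it between consultations falls within the rule's wording. Two analyses with different nulls then stand side by side for the same outcome.

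**Conclusion.** The concern holds in a limited form. A data-driven choice between means and ranks stands beside a regression that does target the mean, and the section does not say which decides. If the mean DRP count is 1 to 3 (an assumption), the gated comparison will usually be Kruskal-Wallis, which does not test a mean change and ignores pairing and clustering. At higher means the choice of test varies with the data.

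The possible conflict is large for Kruskal-Wallis: 30–55% rejection with equal means but unequal spread, and 9–57% power against 70–87% for the paired t test under a proportional fall. For a paired rank test it is small under a proportional fall and larger only if change is unevenly distributed. All these figures assume 138 completers, Poisson or gamma-Poisson counts and no clustering. The sample size of 162 is not called into question. This should be corrected before analysis, but it does not undermine the design.

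**What to change.** Drop the normality pre-test for outcome comparisons. State that the deciding analysis of the number of DRPs is the mean within-patient change, third minus first consultation, with a 95% CI, and that second minus first is handled in the same way. Estimate it from a linear model of the change score with pharmacy-clustered standard errors.

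The model should have no covariates, or mean-centred ones. The current section selects covariates at p<0.2 and then p<0.1, and year of birth is among the patient variables. The intercept of a model with uncentred covariates would describe a patient with every covariate at zero, not the average change.

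Keep medians and percentiles as description, and a paired rank test as a labelled sensitivity analysis.

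The cost is a few sentences and no new data. The downside is small: the mean is more sensitive to a few patients with very large changes, which the medians and the sensitivity analysis would show.

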## Materials and methods

### Study design and setting

A pre-post intervention study with a cluster design and one intervention group will be carried out in Swiss CPs in the canton of Vaud. The study is taking place for 15 months between April 2023 and June 2024 and it will follow the standard protocol items SPIRIT [24] (see Fig 1 and S1 Appendix).

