### Data collection methods

Pharmacists will collect data during their intervention at three time points during the study: at recruitment time, six months later and twelve months after the first encounter. A validated tool will be used for identifying and documenting DRPs, the PharmDISC tool [15] (PharmDISC tool will be used only including the 15 DRPs related to patients’ behavior out of the 24 total DRP). In addition, a questionnaire including seven questions to evaluate patients’ medication knowledge will be used. Pharmacist may choose to complete all documents (medication plan and patients’ medication knowledge questionnaire which are merged in a single document, and, if any DRP is detected, the PharmDISC tool) in paper or electronic version during each consultation with the patient.

Participant pharmacists must complete a sociodemographic questionnaire about CP characteristics and his/her individual characteristics during the educational training. This questionnaire on paper will be collected at the end of the study. In addition, pharmacists should complete an electronic anonymous satisfaction questionnaire after each pharmacist-patient consultation. The time taken per patient to deliver the intervention (differentiated between pharmacist and pharmacy technician time) will be recorded. After coding data, champion pharmacists will send a copy of the data collected to the research team within one month after each consultation and/or contacting the GP when necessary. The research team will evaluate the documents to ensure quality of service provision and fidelity to the study protocol. Pharmacists will receive a remuneration of CHF 100 per pharmacist-patient consultation (which cannot be financed by the basic health insurance) and an additional amount of CHF 10 for the additional time spent on documentation of consultations and interventions for research purposes according to the guidelines given in the educational training. The amount of CHF 100 was calculated by the time expected for each professional involved in the service: approximately 45 minutes for pharmacists (CHF 87 per hour) and approximately 45 minutes for pharmacy technicians (CHF 53 per hour).

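### For comparisons between consultations, the only non-normal test named is Kruskal-Wallis, an independent-groups test that does not fit one group of patients seen three times

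*Protocol article*

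**What the plan says.** Study design and setting describes "A pre-post intervention study with a cluster design and one intervention group". Data collection methods puts the three measurements "at recruitment time, six months later and twelve months after the first encounter". Under Sample size: "Primary objective of the study aims to measure the difference in DRPs per patient observed between consultations".

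Statistical methods and analysis then deals with testing in two consecutive paragraphs.

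- The first is general. "To assess normality, the Kolmogorov Smirnov test will be used", and the rule for comparing continuous outcomes reads: "the T Student’s test or the ANOVA test will be carried out if there is a normal distribution, and Kruskal-Wallis otherwise". It does not say which comparisons are meant. It names no signed-rank, Friedman or other paired non-parametric test.
- The second is specific to the repeated visits. "For each patient, differences between consultations (second and first consultations, third and first consultations) will be compared for dependent variables", with the number of DRPs first among those variables. It continues: "A linear regression model will be performed accounting for the cluster effect". Covariate screening at p<0.2 and then p<0.1 follows. The paragraph does not say which test compares the differences, whether the regression has them as its outcome, or whether it is the primary test.

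**The concern.** The comparison that matters is within patients: one group, three visits. The only test named for non-normal data is built for separate groups of people. DRPs per patient are small whole numbers, probably skewed, so the normality check may well send the primary variable down that route.

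An analyst could then report a Kruskal-Wallis p-value across the three consultations and still be following the text. That test leaves the between-patient variation in the yardstick against which the change is judged. A real fall in DRPs could be missed, and the power behind the 162 patients would not apply to the p-value reported.

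**Working it through.** **The plan's own figure.** The sample size of 162 cannot be reproduced from the article, which gives no standard deviation. It gives a difference of 0.5 DRP, one-tailed 5%, power of at least 0.8, intra-cluster correlation 0.02, 15% dropout and 5 to 10 patients per pharmacy. Solving backwards as a paired comparison:

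- Evaluable patients: 162 × 0.85 = 137.7.
- Design effect 1 + (m − 1) × 0.02: 1.08 at m = 5, 1.18 at m = 10.
- Effective patients: 137.7/1.08 = 127.5; 137.7/1.18 = 116.7.
- Implied SD of the change, 0.5 × √n / 2.487: about 2.27 and 2.17.

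This shows only that a paired calculation is possible. It does not prove that one was used, so 80% power for the paired test is an assumption below.

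**Can Kruskal-Wallis be run on the differences?** Visit 3 minus visit 1 gives one number per patient in one group. The test compares ranks between at least two groups. With one group there is nothing to compare, and the software routine tried returns an error.

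**What happens if it is run across visits?** Take visits 1 and 3, n patients, equal variance σ² at each visit and within-patient correlation ρ (not given in the protocol, so varied).

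- True variance of the mean change: 2σ²(1 − ρ)/n.
- Variance an unpaired test assumes: 2σ²/n.
- The assumed standard error is therefore too large by 1/√(1 − ρ).

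The data remain paired; only the yardstick is wrong. A paired test with 80% power has an expected statistic of 1.645 + 0.842 = 2.487. The unpaired test rejects only when that statistic exceeds 1.645/√(1 − ρ). So:

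- power = Φ(2.487 − 1.645/√(1 − ρ))
- true one-sided error rate = 1 − Φ(1.645/√(1 − ρ))

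| ρ (assumed) | SE ratio | Power | True error rate |
|---|---|---|---|
| 0 | 1.00 | 80% | 5% |
| 0.2 | 1.12 | 74% | 3.3% |
| 0.3 | 1.20 | 70% | 2.5% |
| 0.5 | 1.41 | 56% | 1.0% |
| 0.7 | 1.83 | 30% | 0.13% |

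**Check on Kruskal-Wallis itself.** The formula above is for a test of means. A simulation used skewed counts (gamma-Poisson), 127 patients, an assumed baseline mean of 2.8 DRPs falling by 0.25 at visit 2 and 0.5 at visit 3, two-sided 5%, no clustering and 3,000 runs. Power was:

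| ρ, about | Kruskal-Wallis, visits 1 and 3 | Signed-rank, visits 1 and 3 | Kruskal-Wallis, three visits | Friedman, three visits |
|---|---|---|---|---|
| 0.1 | 63% | 69% | 51% | 50% |
| 0.5 | 36% | 68% | 21% | 47% |
| 0.7 | 13% | 64% | 4% | 43% |
| 0.8 | 3% | 64% | 1% | 40% |

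The levels differ from the first table because the test is two-sided and the data are counts. The pattern is the same: little lost at low correlation, much lost at 0.5 and above.

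**The case against.** The best defence is that the sentence is generic. It sits among descriptive summaries and chi-squared tests and never says that it governs the visit comparison. The next paragraph forms per-patient differences and plans a cluster-adjusted regression; fitted to those differences, that regression keeps the pairing and handles the pharmacies as well. This is a fair reading, and it defeats the stronger inference that the primary result must rest on Kruskal-Wallis. It does not clear the text, which neither makes the differences the outcome of the regression nor calls it the primary test. The covariate screening that follows also allows it to be read as a model of associated factors.

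Three other inferences go too far.

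- A reader might conclude that the t test and ANOVA are wrong too. Both names cover paired and repeated-measures forms, and a condensed article may leave that detail to the full plan.
- A reader might conclude that Kruskal-Wallis has no place here. It is a valid type of test for between-patient comparisons, such as patients who did or did not pre-select their medication, including on change scores (clustering apart).
- A reader might fear a false claim of benefit. With positive correlation, ignoring the pairing pushes the true error rate below 5%. The risk is a missed effect.

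**Conclusion.** Wrong as written, for Kruskal-Wallis in comparisons between consultations only. The named test does not fit one group measured three times: on one set of differences it cannot be computed, and across visits it discards the pairing.

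The size depends on a correlation that the protocol does not give. From an assumed 80% for the paired one-sided test of visit 3 against visit 1, power would be about 70%, 56% or 30% at correlations of 0.3, 0.5 or 0.7, and close to 80% near zero. The loss arises only if the normality check fails and the visit comparison is then reported from Kruskal-Wallis. If the clustered model of within-patient change is in fact primary, the harm is confined to supporting p-values, but the protocol does not say so.

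**What to change.** In Statistical methods and analysis:

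1. State that the primary test is the mean within-patient change in DRPs, estimated from the linear model with pharmacy-clustered standard errors.
2. For comparisons between consultations, specify the paired or repeated-measures forms of the t test and ANOVA. Replace Kruskal-Wallis with the signed-rank test (two visits) or the Friedman test (three visits), as support only, since neither accounts for pharmacy clustering.
3. Keep Kruskal-Wallis and the other independent-group tests for between-patient comparisons, such as pre-selection yes or no.

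The cost is about two sentences. No new data are needed, and the sample size and study conduct do not change.
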